## Abstract

**Background:**

While postpartum depression is a well-researched disorder in mothers, there is growing evidence indicating that some fathers also develop depressive symptoms (paternal postpartum depression, PPD). A recent meta-analysis revealed a total prevalence of paternal depression during pregnancy and up to one year postpartum of 8.4%, with significant heterogeneity observed among prevalence rates. International studies suggest that PPD is characterized by additional symptoms compared to maternal postpartum depression. Furthermore, various risk factors of PPD have been identified. However, the prevalence, symptomatology, risk factors and healthcare situation of fathers affected by PPD in Germany are unknown.

**Methods/design:**

This study comprises a controlled, cross-sectional epidemiological survey administered via postal questionnaires. The primary objective is to compare the prevalence of depressive symptoms in fathers with a 0–12-month-old infant to the prevalence of depressive symptoms in men without recent paternity. Two structurally differing regions (concerning birthrate, employment status, socioeconomic structure, and nationality of inhabitants) will be included. A random sample of 4600 fathers (2300 in each region) in the postpartum period and 4600 men without recent paternity matched by age, nationality and marital status will be assessed regarding depressive symptoms using the PHQ-9. Contact data will be extracted from residents’ registration offices. As secondary objectives, the study aims to provide insights into symptoms and risk factors of PPD in fathers and to assess the current healthcare situation of fathers with PPD in Germany. In an add-on study, genetic and epigenetic mechanisms of PPD will be explored.

**Discussion:**

This study will conduct the first direct comparison between fathers in the postpartum period of one year after childbirth and a matched sample of men without a newborn child. Besides closing this research gap, the findings will provide prevalence estimates as well as insights into specific symptomatology, risk factors, and the current healthcare situation regarding fathers with PPD in Germany. The results will identify low-threshold approaches as a relevant issue for healthcare. Moreover, the findings should inform the development of PPD-specific screening instruments and healthcare offers addressing fathers with PPD.

**Trial registration:**

German Clinical Trials Register (DRKS): DRKS00013339; Trial registration date: August 20, 2018; Universal Trial Number (UTN): U1111–1218-8185.

## Background

While postpartum depression in mothers is a well-researched and recognized mental illness [1], growing evidence suggests that fathers in the postpartum period are also at increased risk of developing depressive symptoms [2–6]. Studies have indicated that the prevalence of depressive symptoms during pregnancy and the postpartum period in fathers is similar to that of mothers [4, 5, 7, 8]. A recent meta-analysis by Cameron et al. (2016) revealed a total rate of depression of 8.4% in fathers during pregnancy and up to one year postpartum, with a higher prevalence of 13% in the 3- to 6-month postpartum period [9]. An earlier meta-analysis by Paulson and Bazemore (2010) yielded a prevalence of 10.4% for depression in fathers during the postpartum period [10]. The authors found that prevalence estimates were moderated by the time of measurement, with higher depression rates of 25.6% during the 3- to 6-month postpartum period [10]. However, due to factors such as study location and methods, prevalence rates vary broadly, ranging from 4 to 25% [4, 10–13]. The varying rates of paternal postpartum depression (PPD) in different countries might be influenced by cultural biases, e.g., differing interpretations of depressive symptoms, social acceptance of mental health problems or divergent expectations with respect to paternal infant care responsibilities. Additionally, methodological aspects such as the use of different diagnostic approaches, biased translations of instruments, or differing sampling methods may also impact PPD prevalence data.

For Germany, there is currently only one longitudinal study by Gawlik et al. (2014), which examined paternal depressive symptoms over the second and third trimester of pregnancy up to 6 weeks postpartum using the Edinburgh Postnatal Depression Scale [14, 15]. The study found that 7.8% of fathers showed depressive symptoms in the postpartum period. Although these findings suggest a scientific and public importance of PPD for Germany, the study only provided information about PPD up to 6 weeks after birth, thus omitting the majority of the postpartum period. Furthermore, the available research is unable to answer the question of whether depressive symptoms are more common in fathers in the postpartum period than in men without a newborn child.

It might be assumed that PPD is characterized by male-specific symptoms [15–17]. Typical symptoms of the so-called “masked men’s depression”, for example, include rage, irritability, emotional rigidity, sleep disorders, and alcohol abuse [18–20]. In the case of PPD, first results point to additional symptoms such as feelings of inadequacy and sadness over “the loss of the old role”, irritability, indecision, impulsivity, violent behavior, avoidance behavior, and substance abuse [21–24]. However, all existing screening and diagnostic instruments for postpartum depression were developed for mothers. As these instruments only cover female-specific symptoms of postpartum depression [25], it is essential to gain distinct insights into the symptoms of PPD.

A starting point to ensure adequate care for fathers is to identify risk factors influencing the emergence and maintenance of PPD. A review by Wee et al. (2006) revealed that PPD is correlated with depressive symptoms in the partner, low relationship quality, and lack of social support [6]. A further study found that a history of severe depression, high prenatal symptom scores for depression, and anxiety were the strongest predictors of paternal depression in the postpartum period [26]. Furthermore, a high rate of comorbid depression and anxiety during the postpartum period has been found in both women and men [27]. According to Bandura [28], self-efficacy plays an important role in regulation of emotional states. High beliefs of self-efficacy make people likely to interpret potential threats as manageable challenges and help them feel less stressed in such situations [29]. In addition, several studies found a relationship between limited mental health and low general self-efficacy [30–34]. Studies also showed that high general self-efficacy beliefs were related to lower levels of depression [35, 36]. This suggests that a lack of general self-efficacy increases the likelihood of developing PPD. Other factors that have been associated with PPD are fears about birth and the father’s role, premature birth, stressful living conditions, previous depressive episodes, impaired sleep, lower socioeconomic status, and influences of cultural and gender roles [3, 10, 23, 37].

A limitation of all existing studies is that findings on prevalence, symptomatology, and risk factors of PPD focus solely on fathers in the first year after childbirth in comparison to historical control data on depressive symptoms. So far, no study has directly compared fathers in the postpartum period of one year after childbirth to a matched sample of men without a newborn child. A simultaneous investigation of depressive symptoms using the same instruments ensures the direct comparability of prevalence estimates between fathers of an infant and men without recent paternity. It provides the benefit of counteracting the risk of over- or underestimation of the relative frequency of depressive symptoms after childbirth, and thus safeguards the scientific quality of the findings. To determine whether having a newborn increases fathers’ likelihood of developing depressive symptoms (compared to not having a newborn), a valid study including a control group is necessary.

The described findings suggest that PPD is a clinically relevant problem for fathers, their families, and the healthcare system, which might currently be under-diagnosed and under-treated [24]. Both in Germany and internationally, men make less use of health care services than women [38, 39]. Traditional concepts of masculinity, feelings of shame, and the issue of stigmatization regarding PPD might prevent men from utilizing adequate treatment offers [40]. Moreover, educational materials, screening procedures, and interventions mostly focus on postpartum depression in mothers, while hardly any information exists for PPD. An increased awareness and knowledge of PPD could facilitate its identification and promote an early and adequate treatment [41]. Dennis and Chung-Lee (2006) found that both informational material and direct conversations promote the utilization of healthcare services among mothers with postpartum depressive symptoms [42]. Providing information on prevalence, symptomatology, and risk factors of PPD might reduce the stigmatization of men dealing with this issue. Therefore, it is important to capture information about the utilization of medical services of fathers suffering from PPD, about access routes in healthcare, and any available treatment offers for PPD. A detailed overview of the current medical care situation for fathers with PPD is necessary in order to offer low-threshold services and foster the implementation of preventive and curative treatment.

In sum, current international research lacks an exhaustive overview of PPD, as it failed to compare the prevalence rate, symptomatology, and risk factors of fathers within one year after childbirth with a matched control group using the same instruments. For Germany, there is no research investigating PPD throughout the entire period of one year after childbirth. Taking into account the international research gaps, this study also closes existing gaps in prevalence, symptomatology and risk factors with a particular focus on Germany. Additionally, knowledge about the healthcare situation of affected fathers can lead to the identification of low-threshold service access in the healthcare system.

## Objectives

The aim of our study is to examine the prevalence of PPD in fathers within the first year after childbirth compared to the prevalence of depressive symptoms in a matched sample of men without recent paternity. We hypothesize that the prevalence of PPD in fathers within one year after childbirth is higher than the prevalence of depressive symptoms in a matched sample of men without recent childbirth. As one of the secondary objectives, we take a closer look at the group of fathers within one year after childbirth to assess differences in PPD prevalence in different time periods. Other secondary objectives are to identify specific symptoms and risk factors of PPD. Furthermore, service utilization regarding PPD is considered as a secondary objective on a healthcare level. In an exploratory add-on study, genetic and epigenetic mechanisms of PPD will be explored.

## Methods/design

### Study design

A controlled, cross-sectional epidemiological survey in men with new paternity within one year prior to this survey (group 1: fathers of an infant) and a matched sample of men without a newborn child within one year prior to this survey (group 2: control group) will be conducted via postal questionnaires. The aim is to compare the prevalence of PPD in fathers within the first year after childbirth to the prevalence of depressive symptoms in a matched sample of men without a newborn child. As study regions, we chose two cities in Southwestern Germany with varying populations regarding birthrate, employment status, socioeconomic structure, and nationality of inhabitants: Freiburg and Mannheim, with 228,000 and 320,000 inhabitants, respectively. As social factors may influence the development of PPD in fathers and of depressive symptoms in men without new paternity, the use of two structurally different cities as study regions allows the generalizability of the results to be investigated.

As primary measure, the Patient Health Questionnaire (PHQ-9) will be used (for detailed descriptions of all instruments used in this study, see below and cf. Table 1). The PHQ-9 is a gender-independent instrument with good psychometric properties [43]. Instead of comparing the results regarding the prevalence of PPD in fathers within one year after childbirth to findings from other studies (historical controls), the data in our study will be compared to a matched sample of men without new paternity one year prior to the survey. This design allows comparative statements to be made, in which the comparison is estimated to be as unbiased as possible, thus increasing the scientific quality of the statements. Furthermore, the date of childbirth and the date of answering the questionnaire will be recorded. From these data, differences in the prevalence rates can be calculated for different time periods after the birth of the child. To assess male-specific symptoms in PPD, the survey will also include the Gotland Male Depression Scale [18]. Moreover, potential risk factors will be considered using various instruments, including the Normative Gender Role Orientation Questionnaire [44], the General Self-Efficacy Scale, and the Social Support Questionnaire [45], as well as self-constructed items (including, e.g., the child’s and mother’s perceived health status). Other potential risk factors include the presence of an earlier depressive episode, the presence of anxiety symptoms, circumstances of pregnancy and childbirth, childcare, as well as demographic factors such as age, marital status, and immigration background. The survey will also cover the healthcare situation and the utilization of obstetric services by fathers with PPD. To record healthcare utilization, the fathers will indicate which services they have used in general and with regard to mental health problems in particular during gestation and since the baby was born (based on different scales, see below and cf. Table 1). Based on the prevalence of PPD and information about healthcare utilization, it will be possible to calculate the rate of fathers who would use specific treatment. The healthcare providers which are commonly contacted during pregnancy and after childbirth (e.g., general practitioner, midwife as part of the aftercare, birth preparation courses) can be used to identify low-threshold service access to adequate healthcare and possibly show important starting points for the implementation of preventive measures or for early interventions in fathers with PPD who are currently under-served.

**Table 1 Tab1:** Objectives and measurements for each group

Objective	Instrument or self-constructed item	No. of items	Group
*Primary objective*			
Depressive symptoms	Patient Health Questionnaire (PHQ-9)	9	both
*Secondary objectives*			
Prevalence differences in different time periods	Date of birth of the child, date on which the questionnaire was filled out	2	fathers of an infant
Specific depressive symptoms	Gotland Male Depression Scale	13	both
Course of depression	regarding the presence and duration of the current episode and previous episodes	5	both
Symptoms of separation anxiety	Adult Separation Anxiety Questionnaire (ASA-27)	27	both
Individuals’ tendency to interpret anxiety-associated physical sensations as threatening	Anxiety Sensitivity Index (ASI)	16	both
Participants’ subjective judgment on their own health status	“How would you describe your health in general?”	1	both
Participants’ subjective judgment on the child’s and the mother’s health status	“How would you describe the health of your infant in general?” “How would you describe the health of the child’s mother in general?”	2	fathers of an infant
Diagnosis of maternal postpartum depression	“Has a doctor or psychotherapist diagnosed postpartum depression in the child’s mother?”	1	fathers of an infant
Extent of perceived self-efficacy	General Self-Efficacy scale (GSE)	10	both
Normative Gender Role Orientation	Questionnaire of Normative Gender Role Attitudes (NGRO)	29	both
Social support	Social Support Questionnaire (F-SozU-K-14)	14	both
Use of support systems	Are you supported by other people or support systems in the care of the newborn?	1	fathers of an infant
Pregnancy and birth	child’s biological father or not; pregnancy was planned, unplanned or unwanted: whether artificial insemination was used or not; complication during pregnancy or birth; premature, miscarriage, or involved multiple births; caesarean section delivery or natural birth; having other children	10	fathers of an infant
Involvement of the father	living in the same household as the infant during pregnancy and after birth; being a single parent; present at the birth; being involved in birth preparation; nighttime care; sleep quality because of the infant; daily time with the infant; use of paternity leave	10	fathers of an infant
Sleep quality in general	“How would you rate your sleep quality in general?”	1	both
Use of medical services	based on scales of the health questionnaire of the study on Adult Health in Germany (DEGS), the German version of the Client Sociodemographic and Service Receipt Inventory (CSSRI-D) and the questionnaire for the collection of health-related resource use in the elderly population (FIMA)	2	both
Use of medical services	the use of health-related offers in the obstetric setting and the use of child-related health offers	2	fathers of an infant
Socio-demographic data	age, marital / relationship status, minimum indicator set for recording migration status, educational level, income status, professional situation	11	both

### Inclusion and exclusion criteria

The study population consists of men from the cities of Freiburg and Mannheim with new paternity within one year prior to this survey (group 1: fathers of an infant) as well as men from the same regions without a newborn child within one year prior to this survey (group 2: control group). The two groups will be matched by age, nationality and marital status. To ensure a high external validity of our results, no exclusion criteria have been established, with the exception of insufficient German language proficiency due to the nature of the survey.

### Recruitment

Contact details of potential study participants for both groups will be obtained from the residents’ registration offices of the chosen study regions of Freiburg and Mannheim, which will enable a random sample of fathers of an infant to be drawn. Due to the random selection of fathers of an infant, a balanced distribution of the children’s age between 0 and 12 months can be expected. Since a request for a sample from the residents’ registration offices takes two days to process, it is guaranteed that all included fathers of an infant will have become a father of a newborn within 12 months prior to this survey. At the same time, the residents’ registration offices of Freiburg and Mannheim will draw the matched control group. The information provided by the residents’ registration offices will include contact details as well as descriptions of the men in the samples according to the variables age, nationality and marital status. After obtaining these sample descriptions, information about the study and a consent form as well as a questionnaire will be sent by post to both groups. The questionnaire is reduced to central variables and a prepaid return envelope will be attached, as these measures are associated with an increased response rate [46].

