### Statistical methods

#### Dealing with dropouts (unit missing)

Based on the data of the residents’ registration offices, it will be possible to describe differences in the composition of the population and the respondents of the two samples (fathers of an infant and control group) in terms of marital status, nationality, and age. The influence of these covariates on the response behavior can be controlled using logistic regressions. If there are significant differences between the population and the respondents of the two samples, a statistical adjustment of these differences will be made in the evaluation.

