#### Sample size calculation

The study will investigate whether a significant difference can be observed between the prevalence of PPD in fathers within the first year after childbirth and the prevalence of depressive symptoms in a matched sample of men without recent paternity. The a priori calculation of statistical power is based on a point prevalence of 5.3% in the control group (95% confidence interval 4.3–6.3%), which corresponds to the incidence of depressive symptoms in men according to the PHQ-9 standard data [48]. Compared to reported prevalence rates, an increase of more than 50% in the point prevalence in fathers of an infant would be relevant. This corresponds to a point prevalence of at least 8.0%. According to the meta-analysis by Cameron et al. (2016), the point prevalence of PPD in fathers in the first year after childbirth lies between 7.2 and 9.6% [9]. Therefore, a potential prevalence of 8.0% is not only a realistic outcome considering the results of previous studies, but would also represent a relevant increase in the rate of depressive symptoms. To be able to detect the difference between the population prevalence of 8.0% in fathers of an infant and 5.0% in the control group with a significance level of 0.05 and a power of 80% in a Chi-square test, data from a total sample size of 2300 participants are necessary.

In Freiburg and Mannheim together, about 5500 children are born each year [61, 62]. Out of these, 4600 fathers of an infant will be randomly selected, meaning 2300 fathers of an infant per city. In addition, a control group (*n* = 4600; 2300 per city) matched according to age, nationality, and marital status will be generated. Thus, a total of 9200 potential participants will be contacted. Based on response rates from other anonymized postal surveys, a dropout rate of about 75% is expected for this study. Already included in these dropout calculations are those men who cannot participate due to incorrect address information. However, the obtained sample size will be sufficiently large to reveal small differences in the prevalence of depressive symptoms among the fathers of an infant (ω = 0.1) for each month after birth with a power > 80% using the Chi-square test.

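### Balanced child ages can be expected among the fathers drawn, not among the quarter expected to respond, and child age is not among the non-response adjustment variables

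*Protocol article*

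**What the plan says.** All references are to the protocol article.

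- **Recruitment** infers from the random draw that "a balanced distribution of the children’s age between 0 and 12 months can be expected". The registration offices supply contact details and "descriptions of the men in the samples according to the variables age, nationality and marital status". The child's date of birth is not listed among these descriptors.
- **Sample size calculation**: "Thus, a total of 9200 potential participants will be contacted", half of them fathers, and "a dropout rate of about 75% is expected for this study". On the sampling frame: "In Freiburg and Mannheim together, about 5500 children are born each year".
- **Dealing with dropouts (unit missing)** compares population and respondents "in terms of marital status, nationality, and age". Where they differ significantly, "a statistical adjustment of these differences will be made in the evaluation".
- **Primary objective** defines the target as prevalence over the whole first year after birth, compared with controls. **Analyses** gives relative frequencies and Chi-square or Fisher's exact tests for nominal outcomes.
- **Prevalence** (under Secondary objectives) has the child's age in weeks calculated from the birth and completion dates, for the comparison of time periods.
- **Background** cites a 2016 meta-analysis giving 8.4% over pregnancy and the first year, "with a higher prevalence of 13% in the 3- to 6-month postpartum period". An earlier meta-analysis gave 10.4% postpartum and 25.6% at 3 to 6 months.

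**The concern.** A random draw fixes the child-age mix of the men contacted. With about one in four replying, the mix that is analysed depends on who replies as well. Table 1 adds up to 138 items for both groups plus 28 for fathers only, 166 in all, and the Discussion concedes that the number of instruments may lower response. It is conceivable that a father's readiness to complete the form changes with the age of the infant.

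If so, a first-year prevalence taken as a simple proportion of respondents gives each child-age period the weight of its response. The listed adjustment variables describe the man and would not correct this directly. Controls have no infant and hence no such mix, so any shift in the fathers' figure passes straight into the primary difference. The dates needed to examine it are already collected from responding fathers.

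**Working it through.** **1. The plan's own figures.** For 8.0% against 5.0%, two-sided 0.05 and 80% power:

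n per group = [1.96 √(2 × 0.065 × 0.935) + 0.842 √(0.08 × 0.92 + 0.05 × 0.95)]² / 0.03² = 1059, or 2118 in total. With the continuity correction it is 1125 per group, 2250 in total, within 3% of the stated 2300.

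Contacts: 9200 × 0.25 = 2300 respondents; 4600 × 0.25 = 1150 fathers, about 96 per month of child age. The draw takes 4600 / 5500 = 84% of a year's births, so balance among the men drawn is a sound expectation.

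**2. Prevalence outside the peak.** Take 3 to 6 months as one quarter of the year.

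- 2016 meta-analysis: (0.084 − 0.25 × 0.13) / 0.75 = 0.0687
- Earlier meta-analysis: (0.104 − 0.25 × 0.256) / 0.75 = 0.0533

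The 8.4% includes pregnancy, so the first value is approximate.

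**3. Effect of uneven response.** Let r be the response at 3 to 6 months relative to the other months. The documents give no value for r; the range below is an assumption. The stratum's share of respondents is w = 0.25r / (0.25r + 0.75), and the crude prevalence is w × peak + (1 − w) × other.

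| r | w | 13% / 8.4%: crude | shift (points) | 25.6% / 10.4%: crude | shift (points) |
|---|---|---|---|---|---|
| 0.5 | 0.143 | 7.74% | −0.66 | 8.23% | −2.17 |
| 0.8 | 0.211 | 8.16% | −0.24 | 9.60% | −0.80 |
| 1 | 0.250 | 8.40% | 0 | 10.40% | 0 |
| 1.25 | 0.294 | 8.67% | +0.27 | 11.29% | +0.89 |
| 2 | 0.400 | 9.32% | +0.92 | 13.44% | +3.04 |

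**4. Yardstick.** The standard error of the planned difference is √[(0.08 × 0.92 + 0.05 × 0.95) / 1150] = 0.0103, about 1.0 point. The planned difference is 3.0 points.

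**5. Cost of reweighting.** Variance inflation is the sum over strata of (target share)² / (respondent share).

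- r = 0.5: 0.25² / 0.143 + 0.75² / 0.857 = 1.09, and the same for r = 2. For r = 0.67 or 1.5 it is 1.03. The effective number of fathers is therefore 1051 to 1115 of 1150.
- Delay between draw and completion will thin out the first month of life. Suppose, as an illustration, that it is one-quarter filled and the other eleven months are equal (total 11.25 units). Twelve equal monthly weights give (1/144) × (45 + 11 × 11.25) = 1.17. Four three-month bands, with respondent shares of 0.200 and three times 0.267, give (1/16) × (5 + 3 × 3.75) = 1.02.

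**The case against.** The case against is substantial, and much of it stands.

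- The sentence stands under Recruitment and describes the draw. Read that way it is correct. A reader might infer that the article asserts balance among respondents; it does not say so.
- Nothing in the article shows that response depends on the infant's age. Both the mechanism and the range of r are assumptions, and the direction is open.
- A reader might take −2.2 to +3.0 points as the likely error, as large as the planned difference. The article does not support that. The scenario implies 5.3% in the other nine months, which is the control prevalence quoted in the sample size section, and so assumes almost no excess outside months 3 to 6. The Background also attributes varying rates to study location and methods, so pooled subgroup figures are not an age profile within one population. The sample size section relies on the 2016 meta-analysis, for which the shifts stay below one standard error of the difference even at r = 0.5 or 2.
- A reader might also infer that the crude proportion is fixed as the only primary estimate. The article provides for adjustment and for logistic regression on other influencing factors, and a fuller analysis plan may exist.
- Prevalence by time since birth is a secondary objective, so an uneven mix could be noticed.

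What remains is narrower. The reason given for balance does not reach the respondents, the adjustment variables that are named leave out child age, and the recorded dates are assigned to a secondary question only.

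**Conclusion.** The point holds as a moderate one. The expected balance applies to the 4600 fathers drawn and not, without a further assumption, to the roughly 1150 respondents; the stated non-response adjustment does not cover child age.

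On the figures closest to the plan's design, the first-year prevalence would shift by about −0.2 to +0.3 points for moderate response differences and −0.7 to +0.9 points for large ones, against a standard error of about 1.0 point and a planned difference of 3.0. More extreme pooled figures give larger shifts, but they are a poor guide here. All of this assumes that response varies with child age, that months 3 to 6 make up a quarter of the year, and that 8.4% is an adequate stand-in for the postpartum average. With equal response the shift is zero. This justifies a check on the primary comparison, not a replacement for it.

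**What to change.** 1. In Recruitment, limit the statement on balance to the fathers contacted.
2. Report the child-age distribution of responding fathers.
3. Add a sensitivity analysis of the primary comparison, stated before it is run. Post-stratify the fathers' prevalence to equal weights for four three-month child-age bands, using the recorded birth and completion dates, or to the registry's birth distribution if the offices can supply it. Present it beside the planned estimate. State in advance how infants who have passed 12 months by completion are assigned.

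Three-month bands are preferable to single months because equal monthly weights would up-weight a first month thinned by postal delay.

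The cost is a little analysis and about 2% to 9% variance inflation; no new data are needed unless the registry distribution is used. Trial status reports data collection as finished and analysis as ongoing, so this is still within reach. It corrects the child-age mix only. Response that depends on depression itself is untouched and remains under the general selection-bias caveat in the Discussion.
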